## Abstract

**Background:**

Remote ischemic conditioning (RIC) refers to the application of repeated short periods of ischemia intended to protect remote areas against tissue damage during and after prolonged ischemia.

**Aim:**

We aim to evaluate the efficacy of RIC, determined by the modified Rankin Scale (mRS) score at 90 days after stroke onset.

**Design and methods:**

This study is an investigator-initiated, multicenter, prospective, randomized, open-label, parallel-group clinical trial. The sample size is 400, comprising 200 patients who will receive RIC and 200 controls. The patients will be divided into three groups according to their National Institutes of Health Stroke Scale score at enrollment: 5–9, mild; 10–14, moderate; 15–20, severe. The RIC protocol will be comprised of four cycles, each consisting of 5 min of blood pressure cuff inflation (at 200 mmHg or 50 mmHg above the systolic blood pressure) followed by 5 min of reperfusion, with the cuff placed on the thigh on the unaffected side. The control group will only undergo blood pressure measurements before and after the intervention period. This trial is registered with the UMIN Clinical Trial Registry (https://www.umin.ac.jp/: UMIN000046225).

**Study outcome:**

The primary outcome will be a good functional outcome as determined by the mRS score at 90 days after stroke onset, with a target mRS score of 0–1 in the mild group, 0–2 in the moderate group, and 0–3 in the severe group.

**Discussion:**

This trial may help determine whether RIC should be recommended as a routine clinical strategy for patients with ischemic stroke.

## Introduction

In recent years, hyperacute reperfusion treatment has progressed remarkably due to the establishment of recombinant tissue-type plasminogen activator (rt-PA) and endovascular treatment (EVT) (1, 2). Although Japan is proceeding with a plan to accelerate the development of an efficient care system for stroke patients (forming new stroke centers and stroke care units), only 6–8% of patients can receive hyperacute reperfusion therapy (3). In Japan, edaravone has been used as an effective method to reduce ischemic insults. However, it is not widely used internationally; it has yet to demonstrate sufficient efficacy (4).

Remote ischemic conditioning (RIC) is a therapeutic strategy in which several cycles of brief focal ischemia, followed by reperfusion in the arms or legs, confer protection against the more severe detrimental effects of ischemia in target organs (5–8). Although the underlying mechanisms are not fully understood, current evidence indicates that RIC reduces inflammation, oxidative stress, and cerebral edema, mediated by humoral, immunoregulatory, and neurotrophic factors (9). Although the clinical application of RIC in patients with acute ischemic stroke has been attempted, its efficacy has not yet been validated (10–12). Moreover, no clinical trials have been conducted on acute ischemic strokes in Japan.

One reason for the inability to confirm the efficacy of RIC in previous studies may be the use of a unified definition of a good outcome as assessed by the modified Rankin Scale (mRS), regardless of the neurological severity of the enrolled patients upon admission. Another reason may be the lack of an established RIC protocol. Therefore, this study aims to evaluate the efficacy of an RIC protocol based on recent literature, determined by the mRS score at 90 days after stroke onset, with a good outcome defined according to the severity at enrollment.

## Methods and analysis

### Design

Remote Ischemic Conditioning for Acute Ischemic Stroke (RICAIS) part 2 is an investigator-initiated, multicenter, prospective, randomized, open-label, parallel-group clinical trial targeted at patients with acute ischemic strokes. The protocol is registered with the UMIN Clinical Trial Registry (UMIN000046225).

### Patient population

We will recruit patients diagnosed as having had an acute ischemic stroke *via* brain MRI and/or CT. All 14 Japanese stroke centers and their prehospital regional centers will be invited to participate. The inclusion and exclusion criteria are listed in Table 1, and the baseline assessments and study procedures are provided in Table 2 and Figure 1. Participants need to show a defined ischemic lesion on magnetic resonance imaging (MRI). Patients who received alteplase treatment or mechanical thrombectomy can be enrolled 12 h after the intervention. All patients will provide written informed consent in the acute phase. If the research participant is an adult who is objectively judged to lack the capacity to give informed consent due to a speech or writing impairment caused by a stroke, the consent may be obtained from the legal representative.

**Table 1 T1:** Inclusion and exclusion criteria.

**Inclusion criteria**	**Exclusion criteria**
• Patients hospitalized in participating institutions	• mRS >2 before stroke onset
• Male and female patients (age range, 20–90 years)	• Planned intravenous rt-PA and/or EVT after registration
• Diagnosed as acute ischemic stroke by performing brain MRI and/or CT	• Within 12 h after rt-PA administration or EVT
• Within 48 h after stroke onset	• Systolic blood pressure ≥180 mmHg
• NIHSS scores range from 5 to 20 at registration	• History of PAD
• Tolerance to systemic blood pressure measurement and systolic blood pressure <180 mmHg	• Pregnant patients or patients suspected of being pregnant
	• Patients deemed unsuitable as participants by the investigator

CT, computed tomography; EVT, endovascular treatment; MRI, magnetic resonance imaging; NIHSS, National Institutes of Health Stroke Scale; PAD, peripheral arterial disease; rt-PA, recombinant tissue-type plasminogen activator.

**Table 2 T2:** Study procedures for eligible patients with acute ischemic stroke.

**Procedures/Data collection**	**Screening (days 0–1)**	**Registration/ Baseline visit 1 (day 1)**	**Visit 2 (day 3)**	**Visit 3 (day 7)**	**Visit 4 (day 30 or discharge)**	**Visit 5 (day 90 ±14 days)**

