**Biomarkers**						
Blood biochemistry	×		×	×		
Brain CT or MRI scan	×			×		

CT, computed tomography; MRI, magnetic resonance imaging; mRS, modified Rankin Scale; NIHSS, National Institutes of Health Stroke Scale; RIC, remote ischemic conditioning.

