### Statistical analysis

The target populations for analysis will be defined as follows. The full analysis set (FAS) will comprise all randomized participants, with the exclusion of those who never received any protocol treatment, those who underwent at least one protocol treatment but whose post-protocol data are not available, and those who did not meet the eligibility criteria. The intention-to-treat population will comprise all subjects who underwent randomization. The per-protocol set will comprise those in the full analysis set, with the exclusion of subjects with remote ischemia and poor conditioning compliance (<80%). The population for the safety analysis will comprise all subjects who received at least one protocol treatment.

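### The eligibility text requires an ischemic lesion on MRI, but Table 1 accepts MRI and/or CT, and the full analysis set drops patients judged ineligible

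*Protocol article*

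**What the plan says.** All references are to the protocol article.

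- **Patient population, opening sentence:** "We will recruit patients diagnosed as having had an acute ischemic stroke", with MRI, CT or both allowed as the means of diagnosis.
- **Patient population, location of the criteria:** "The inclusion and exclusion criteria are listed in Table 1".
- **Table 1, inclusion:** "Diagnosed as acute ischemic stroke by performing brain MRI and/or CT". No item in Table 1 asks for a visible lesion or makes MRI compulsory.
- **Patient population, later sentence:** "Participants need to show a defined ischemic lesion on magnetic resonance imaging (MRI".
- **Table 2, Biomarkers:** one row, "Brain CT or MRI scan", marked at screening and at day 7.
- **Statistical analysis, FAS:** among those left out of the randomised participants are "those who did not meet the eligibility criteria".
- **Statistical analysis, other sets:** "The per-protocol set will comprise those in the full analysis set", less those with poor compliance. Separately, "The intention-to-treat population will comprise all subjects who underwent randomization".
- **Randomization:** only the physician who rates the 90-day mRS is kept unaware of the arm. All other staff can see the arm and the test results.

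**The concern.** An eligibility rule should give the same answer wherever it is read. Here a site working from Table 1 and a site working from the text would enrol different patients, so the target population is not fixed.

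The mismatch goes further than enrolment because eligibility is also a condition of membership in the FAS. A patient admitted in good faith under Table 1 could later be declared ineligible under the text and taken out. The trial is open-label apart from the mRS rating, so that decision would be made by people who know the allocation. A rule with two readings, settled after allocation, leaves room for exclusions that differ between arms.

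**Working it through.** The plan states no figure on this point, so the check sets the passages side by side.

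**Step 1: apply each rule to the same patients.**

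| Patient with a stroke diagnosis | Table 1 | MRI-lesion sentence |
|---|---|---|
| MRI shows a lesion | meets | meets |
| CT only, no MRI done | meets | fails |
| MRI done, no lesion visible | meets, since Table 1 asks for a diagnosis by imaging and not for a lesion | fails |

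The CT-only patient is the clearest case. The lesion-negative case depends on reading Table 1 as it stands, without adding a lesion requirement to it.

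**Step 2: see whether the rules can be read together.** The joint reading is that stroke is diagnosed by either modality and an MRI lesion must then be shown as well. Under it, CT alone never suffices, so the CT option in the opening sentence and in Table 1 has no effect. A compulsory criterion is also missing from the table said to list the criteria, and a site that follows the Table 2 screening entry may hold no MRI on which to judge it. The joint reading can be applied, but only by overriding other statements in the article.

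**Step 3: follow the second and third patients into the analysis sets.**

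| Set | Only Table 1 counts as eligibility | MRI-lesion sentence also counts |
|---|---|---|
| FAS | kept | removed |
| Per-protocol (subset of the FAS) | kept if compliant | removed |
| Intention-to-treat | kept | kept |
| Safety (at least one protocol treatment) | kept if treated | kept if treated |

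The two readings differ in the FAS and the per-protocol set only. Neither the Statistical analysis section nor the section on the primary outcome says which set is used for the Chi-square test.

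**Step 4: check the timing.** Table 2 puts imaging at screening, in the same column as randomisation, and again at day 7, after treatment has begun. The MRI-lesion sentence does not say which scan counts. Nothing on this point ties the eligibility judgement to images obtained and read before allocation.

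**The case against.** The strongest reply is that this is a drafting omission. The article names Table 1 as the list of criteria, so the FAS exclusion can be read against Table 1 alone, and a CT-diagnosed patient then stays in. The Table 2 row also covers follow-up imaging and need not define how patients are enrolled. Both remarks are fair. They show that one reading does no harm, but not that it is the reading in force: the sentence is worded as a requirement on participants. A fuller protocol could settle which rule is meant, but it could not make both statements in the article true.

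Four stronger readings are tempting, and the document does not support them.

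- **That the primary result is affected.** This holds only if the FAS is the primary set. The article does not say so, and it defines an intention-to-treat set that keeps these patients.
- **That the exclusions will differ by arm.** The article describes no retrospective review of imaging, and the screening scan precedes the first treatment visit. Open access to allocation makes biased reclassification possible and no more than that.
- **That the sample size margin is used up.** A reader might compare the 400 enrolled with the 334 required and subtract patients removed on imaging. The article gives no share of CT-only or lesion-negative patients, so any loss of power would rest entirely on an assumed share. The 10% drop-out allowance gives withdrawal and loss to follow-up as examples, so ineligibility is not shown to lie outside it.
- **That the FAS definition makes the wording mismatch graver in itself.** Removing ineligible randomised patients is a separate choice that would exist even with consistent wording. It matters here because it carries the ambiguity into the analysis.

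**Conclusion.** The contradiction is real: the section and its own table give different imaging criteria, and the joint reading does not remove the conflict. The certain consequence is an unclear enrolled population. The conditional consequence is that, if the MRI-lesion sentence counts as an eligibility criterion, patients who meet Table 1 can be dropped from the FAS and the per-protocol set after allocation. The primary analysis is touched only on the further condition that the FAS is its basis. The size cannot be calculated, because the article does not say how many patients would be diagnosed without an MRI lesion. The point should be corrected, and it rests on the wording and on the risk of selective exclusion, not on power.

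**What to change.** Reconcile the Patient population text, Table 1 and Table 2 to one imaging criterion. Either the MRI lesion becomes an item in Table 1 and the screening row is changed to match, or the sentence is removed from the text. The choice is the sponsor's.

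State that the criterion is judged on imaging obtained and read before randomisation, and record the judgement at that time. State also that no randomised patient leaves the primary analysis set because of imaging read or reinterpreted after allocation.

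The cost is a wording change and one field on the pre-randomisation checklist. The downside is that a few patients without a visible lesion may stay in the analysis, which could dilute a true effect slightly.

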**Enrollment**						
Informed consent	×					
Demographic characteristics	×					
Confirmation of patient background and medical history	×					
Randomization	×					
**Intervention**						
RIC		×	×	×		
**Assessment**						
Concomitant medication confirmation	×	×	×	×	×	×
Physical examination (including height and weight)	×					
Vital signs	×	×	×	×	×	×
Systolic blood pressure measurement of the upper and lower limbs	×	×	×	×		
NIHSS	×	×	×	×	×	
mRS	×				×	×
Questionnaire and pain scale	×	×	×	×	×	×
Description for the case report form	×	×	×	×	×	×
Confirmation of adverse events	×	×	×	×	×	×
Electrocardiogram	×			×		×
**Biomarkers**						
Blood biochemistry	×		×	×		
Brain CT or MRI scan	×			×		

CT, computed tomography; MRI, magnetic resonance imaging; mRS, modified Rankin Scale; NIHSS, National Institutes of Health Stroke Scale; RIC, remote ischemic conditioning.

**Figure 1 F1:**
[figure not shown]
Trial design flowchart.

### Randomization

The patients will be divided according to their National Institutes of Health Stroke Scale (NIHSS) score at enrollment: 5–9, mild; 10–14, moderate; 15–20, severe. Randomization will be performed using a predefined table generated by a computer program, and the results of the assignment will be immediately sent to the physician in charge *via* a computer. To eliminate bias, the assigned study groups will not be disclosed to the evaluating physician during evaluation of mRS at 90 days post stroke. All other staff will have access to the study arm and test results of the participants.

### Intervention

For all patients, a manual blood pressure cuff will be placed around the lower leg or thigh of the unaffected side, and blood pressure will be measured while detecting the dorsalis pedis artery using an ultrasonic Doppler blood flow meter. The intervention (RIC) group will receive four cycles of 5 min of blood pressure cuff inflation, followed by 5 min of reperfusion. Cuff inflation in the RIC group will be set at 200 mmHg or 50 mmHg above the systolic blood pressure; however, if the patient cannot tolerate this, the cuff pressure may be reduced to 180 mmHg. This procedure will be performed once daily after enrollment, for a minimum of 3 days and a maximum of 7 days. In contrast, the control group will only undergo blood pressure measurements before and after the intervention period (the 40-min duration required for four cycles of RIC). Discomfort and pain will be assessed using a verbal rating scale ranging from 0 to 4 (0, no pain; 1, mild pain; 2, moderate pain; 3, severe pain; 4, very severe pain) (13).

### Primary outcome

The primary outcome will be a good functional outcome at 3 months after stroke onset, with a target mRS score of 0–1, 0–2, and 0–3 in the mild, moderate, and severe groups, respectively. The mRS scores will be determined by face-to-face assessments or structured telephone interviews performed by various assessors, who will be blinded to the allocation results.

### Secondary outcomes

The secondary outcomes will be the proportion of patients with good functional outcome (assessed by the mRS) in each group at 3 months after stroke onset; change in NIHSS scores from before RIC to after RIC; incidence of major adverse cardiovascular events (MACE), aspiration pneumonia, and all-cause mortality within 90 days after stroke onset; frequency of adverse RIC-related events; and proportion of patients with an mRS score of 0–1.

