### Statistical analysis of secondary outcomes

Percentage differences between the RIC and control groups in terms of the incidence of MACE, aspiration pneumonia, frequency of adverse RIC-related events, and all-cause mortality within 90 days will be evaluated using the Chi-square test. The change in NIHSS score from the time of enrollment to 1 week later will be evaluated in a two-sided analysis of variance, with α = 0.05 and power = 0.80. Additionally, with stratified analysis, we will compare the differences in the achievement rate (percentage) of the primary outcome in the RIC and control groups according to the severity of the disease at the time of enrollment (mild, moderate, and severe groups), age (dichotomized by the median of all enrolled patients), sex, presence of occlusion or severe stenosis of the main cerebral artery, treatment with rt-PA and/or EVT, and presence of diabetes mellitus.

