
The primary outcome of this trial will be good functional outcome at 3 months, determined by the mRS score. In most previous studies, the definition of a good functional outcome at 3 months (based on the mRS) was the same for all patients, regardless of the NIHSS score at stroke onset. Our study differs from previous studies in this respect. Referring to previous studies showing the relationship between NIHSS at admission and mRS at discharge or 3 months after stroke onset, our study will divide patients into three groups based on their neurological severity (assessed by the NIHSS) at enrollment into the trial and will use different target mRS scores to define a good outcome at 3 months according to the severity group. For the safety outcome, the analysis will be based on the entire randomized sample. This approach has been used in a recent comparative study and is considered reasonable given the excellent safety profile of RIC.

Finally, we aim to include 400 patients. In this study, the criteria were simplified to enroll a more significant number of patients with various types of strokes. Therefore, given that ~200 patients with ischemic stroke are admitted to our hospital each year, and since this is a multicenter study, we expect to be able to recruit 400 patients during a recruitment period of 2 years.

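### MACE and aspiration pneumonia are counted from stroke onset rather than randomisation, and an early final visit leaves up to 14 of the 90 days without scheduled contact (minor; secondary outcomes only)

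*Protocol article*

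**What the plan says.** All references are to the protocol article.

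- **Event window.** Secondary outcomes lists "incidence of major adverse cardiovascular events (MACE), aspiration pneumonia, and all-cause mortality within 90 days after stroke onset".
- **Entry.** Table 1 (Patient population) admits patients "Within 48 h after stroke onset". For those who had reperfusion treatment, the text adds: "Patients who received alteplase treatment or mechanical thrombectomy can be enrolled 12 h after the intervention".
- **Visits.** Table 2 labels entry "Registration/ Baseline visit 1 (day 1") and the last scheduled contact "Visit 5 (day 90 ±14 days"). The row "Confirmation of adverse events" is ticked in every column, Screening included.
- **Analysis.** Statistical analysis of secondary outcomes compares simple percentages. It states that "all-cause mortality within 90 days will be evaluated using the Chi-square test", and applies the same test to MACE and aspiration pneumonia. It gives no origin for the 90 days.

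No section limits these outcomes to events after randomisation. None says how status to day 90 is established when the last visit is held earlier.

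**The concern.** **Start of the window.** The clock runs before the patient is in the trial. A pneumonia or cardiovascular event in the hours between onset and allocation meets the definition as written. For patients treated with rt-PA or EVT, a pre-randomisation interval of at least 12 h is built in. RIC starts after enrolment, so it can neither cause nor prevent these events. Counting them in both arms pulls the comparison towards no difference. That matters for a benefit on pneumonia, and equally for a harm that the trial would want to see.

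**End of the window.** A ±14-day window is ordinary for reading the mRS at about three months. It fits a cumulative 90-day event count less well. A patient whose last scheduled contact is on day 76 has not been observed through day 90, but a simple proportion treats that patient as fully followed.

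**Working it through.** The article states no event rates and no power for these outcomes, so there is no figure of its own to reproduce on this point. The one stated calculation is the primary sample size. It reproduces with 35% against 50%, two-sided 5%, 80% power and unpooled variance: (0.35×0.65 + 0.50×0.50) × (1.960 + 0.842)² / 0.15² gives 167 per arm, 334 in total. Nothing below changes it.

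**1. Start of the window**

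- Latest entry is 48 h, or 2 days, after onset (Table 1).
- The share of the window that can precede randomisation is at most 2/90 = 2.2% of the days.
- The share of *events* that precede randomisation, f, is unknown. It exceeds 2.2% if pneumonia or MACE cluster in the first days, which is an assumption.

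If the true risk ratio is R for events after randomisation and 1 for those before it, the observed ratio is f + (1 − f)R. As an illustration, assume R = 0.6 and 200 patients per arm:

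| f | Observed risk ratio | Power, control risk 20% | Power, control risk 10% |
|---|---|---|---|
| 0 | 0.60 | 59% | 31% |
| 2.2% | 0.61 | 57% | 30% |
| 10% | 0.64 | 49% | 26% |
| 30% | 0.72 | 32% | 17% |
| 50% | 0.80 | 18% | 10% |

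The control risks, R and f are all assumed. The table shows direction and range; it does not estimate the effect in this trial.

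**2. End of the window**

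- Earliest final visit: 90 − 14 = day 76. Latest: 90 + 14 = day 104.
- Unscheduled remainder for the earliest visit: 14/90 = 15.6%.
- The zero point of the day count in Table 2 is not stated. If registration is day 1, day 76 lies 75 days after registration. That is 75 to 77 days after onset for an entry lag of 0 to 2 days, and the remainder becomes 13 to 15 days.

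Assume a 90-day risk of 10% at a constant rate:

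- Risk observed to day 76 = 1 − 0.90^(76/90) = 8.5%.
- Shortfall against full follow-up = 10.0 − 8.5 = 1.5 percentage points.

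This is the largest shortfall under that model, and it applies only to a patient seen on the earliest permitted day. If risk is concentrated early, days 76 to 90 carry less of it and the shortfall is smaller.

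**The case against.** The strongest reply is that this is a wording matter on secondary outcomes with no stated power basis. Anchoring at onset matches the clock of the primary outcome, and a fixed 90-day proportion is conventional. The entry limit and visit window are the same in both arms, and randomisation balances pre-entry events in expectation. Table 2 already collects medical history at Screening. Its adverse-event tick there is data collection; it does not say that what is found then counts as an outcome. Ascertaining events after an early visit may be set out in the full protocol, which a journal article condenses. All of this stands, and it keeps the point minor. It does not remove the literal effect of the outcome definition.

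Four stronger readings are tempting, and the documents do not support them:

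- **That deaths before randomisation count.** They cannot. For death, the onset anchor only shortens the time at risk after randomisation, by up to 2 days.
- **That a visit as late as day 104 inflates the count.** Under the constant-rate model, a reader might set 8.5% at day 76 against 1 − 0.90^(104/90) = 11.5% at day 104 and see a 3-point spread. Events on days 91 to 104 already lie outside the definition, so a patient seen on day 104 contributes 10%, and the spread is at most about 1.5 points.
- **That late events are lost.** They may be missed only in patients seen before day 90. Visit 5 is the last scheduled visit; no section calls it the last possible contact.
- **That open-label staff will time visits differently by arm and so bias the result.** Staff other than the 90-day mRS evaluator can see the arm, but nothing in the text indicates differential timing. Even if one arm averaged day 83 and the other were followed to day 90, the model gives 1 − 0.90^(83/90) = 9.3% against 10.0%.

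**Conclusion.** The point holds as a minor one. As written, MACE and aspiration pneumonia arising between onset and randomisation count as outcomes, over an interval of up to 48 h. Separately, patients whose final visit precedes day 90 enter a 90-day proportion with up to 14 days (15.6%) after their last scheduled contact.

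The expected result is dilution and noise in secondary outcomes, not a shift in favour of either arm. The size of the first effect depends on the share of events that precede randomisation, which the documents do not give. The second is at most about 1.5 points per patient if the 90-day risk is 10% at a constant rate. The primary outcome, its analysis and the sample size are unaffected.

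**What to change.** 1. **Secondary outcomes and their statistical analysis:** count MACE, aspiration pneumonia and death from randomisation to day 90, and use the same wording in both places. State once what day 90 is counted from. Record conditions already present at randomisation as medical history.
2. **Table 2:** when Visit 5 falls before day 90, confirm event and vital status on or after day 90. The structured telephone interview already allowed for the mRS could serve.

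With status confirmed in this way, the chi-square test can stay. A cumulative-incidence comparison with censoring at last contact is an option, not a necessity.

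The cost is a few words in two sections, a short extra call for patients seen early, and slightly fewer counted events. The events removed are ones that allocation could not have influenced.
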